### Analysis strategy regarding the secondary study aims

The strategy for the secondary aims entails data collection and analysis of quantitative and qualitative data from the EEG, questionnaires, a behavioral task, and a semi-structured interview. To analyze the effects of an MT program (GMT/IMT) in addition to ST compared to ST only on secondary dependent variables, descriptive, graphical, and inferential analyses will be used. Effect sizes will also be computed where relevant. The present research is a feasibility study and because of the small sample size, certain inferential statistics requirements cannot be satisfied. Therefore, results related to the secondary aims are to be considered—and will be presented as—preliminary. Descriptive analyses will be conducted by calculating means and standard deviations at each time point. Inferential statistical analyses will be conducted to evaluate the effect of MT (GMT/IMT) in addition to ST on mental health and brain processing by comparing the data between pre- and post- intervention in each group using a parametric or non-parametric test (e.g., paired t-test or Wilcoxon Signed-Rank test, respectively) depending upon the data distribution. The dependent variables that we will measure are pre-post intervention changes in the following outcomes: (I) score of the PHQ-9 and resting-state FAA for depressive symptoms; (II) score of the BSCS and resting-state beta frequency band for the craving state experienced over a 24-h period; (III) score of the GAD-7 and resting-state FMT for anxiety symptoms; (IV) score of the TOP for substance use, days of primary substance used, average usage of primary substance per day, physical wellbeing health, psychological health, and overall quality of life; and (V) P3 EEG event-related potential amplitude and behavioral accuracy during a Go/No-Go task for the inhibitory control. The statistical procedure to analyze data from pre-post intervention questionnaires involves both within-subject (or repeated-measures design) and between-groups (or independent design). Indeed, a pre-post intervention comparison of scores from the questionnaires will be performed for each group (GMT, IMT and ST) with a paired-samples t-test. In case the assumptions of normality and homogeneity of the data will be violated, a non-parametric Wilcoxon Signed-Rank test will be performed. The difference scores obtained from this repeated-measures design, will be used for the independent design analysis: pre-post intervention difference scores in the questionnaires administered to the MT groups (GMT and IMT) will be compared with pre-post intervention difference scores in the questionnaire administered to the ST group utilizing independent t-test. In case the assumptions of normality and homogeneity of the data will be violated, a non-parametric Mann–Whitney test will be performed.

For the resting-state EEG data (alpha—FAA -, beta, and theta—FMT—bands) pre-post intervention comparisons will be performed utilizing z-scores from a Normative EEG database (NG software) [54]. Furthermore, to represent the pre-post intervention difference in the topographic distribution of EEG power in the selected frequency bands a paired-samples t-test will be performed for each of the three groups. If deviations from normality will be found in the data, a non-parametric Wilcoxon Signed-Rank test will be performed. Between-group power differences will be calculated as well, by comparing differences in the topographic distribution of the EEG power in participants who received MT (GMT and IMT) alongside ST vs participants who received ST only through an independent t-test. If deviations from normality will be found in the data, a non-parametric Mann–Whitney test will be performed. Relationships between changes in the pre-post intervention questionnaire scores (PHQ-9, GAD 7, BSCS, VAS, HAQ-II) and changes in the respective EEG measures (see above) will be tested using Pearson's correlation coefficients with 95% confidence interval [16]. Likewise, we will implement the same correlation procedure to test the relationship between pre-post intervention changes in inhibitory control (P3 ERP amplitude and accuracy on “no-go” trials) and changes in the scores of the Brief Substance Craving Scale. Changes in the pre-post MT (GMT and IMT) sessions scores from the craving thermometer will be analyzed graphically (i.e., scatterplot). Those who attend more than two sessions but disengage before the study ends will have the measures up to the point of their disengagement included in data analysis.

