**Methods:**

Fifteen participants, from a community service based in London, will take part in a mixed-methods non-blind randomized-controlled trial. Ten participants will receive six-weekly sessions of music therapy in addition to the standard treatment offered by the CSMTS—five of them will receive individual music therapy and five of them will receive group music therapy—while a further five participants will act as a control group receiving standard treatment only.

Satisfaction and acceptability will be evaluated in focus groups with service users and staff members following the final treatment session. Moreover, attendance and completion rates will be monitored throughout the intervention. Subjective and behavioral indexes will be assessed before and after the interventions to explore the effects of music therapy on craving, substance use, symptoms of depression and anxiety, inhibitory control, and will be correlated with associated neurophysiological signatures. In-session analysis of two individual music therapy sessions will serve to explore how music and emotion are processed in the brain within the therapy. The data collected at each step will be included in an intention-to-treat analysis basis.

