The staff cohort will be recruited by directly approaching staff members who were involved in the project or may be involved in future forms of the program. This will be done by emailing them directly or attending staff meetings and asking for volunteers to participate. Staff members will also be invited to attend the drop-in session. SUs who participate will be rewarded Capital Card^®^ points. Points will be awarded for each session completed, including the focus group and interview. WDP Capital Card^®^ is a reward card scheme to help SUs with their recovery journey ([35]; https://www.wdp.org.uk/the-capital-card). Where the project has issues recruiting the full number of 15 SU participants, we will extend the recruitment window to 2–3 months and we will re-run the drop-in session to attract more SUs. We will also contact WDP key workers to promote the study. Recruitment for GMT will continue until 5 participants are recruited and allocated to this group. If the 5 participants are not recruited within 2 months, the GMT sessions will start once at least 3 participants have been allocated. The GMT will continue while 3 participants remain in the study. The start of the IMT sessions will be staggered: SUs allocated to the IMT group will start their MT sessions within 1–2 weeks of being allocated to this group. If a participant in the IMT group drops out within the first 2 weeks, we will re-recruit and the new participant will start from week 1. We will only re-recruit twice before continuing with the remaining IMT participants. If after 3 months, the project does not have enough participants to go ahead, the research team will discuss additional recruitment strategies, widening the inclusion/exclusion criteria or a possible change in study location. The research team will take any feedback from SUs or staff around recruitment and incorporate where necessary. Where a participant decides to withdraw from the study, they will be provided an exit survey and withdrawal confirmation form. This form gives the participant the option to decide if the data collected up to their withdrawal will be kept and used in the final analysis or destroyed and not used in the final analysis. If they choose not to complete this survey or ask that all their data collected up to their withdrawal is deleted, the exit survey will be destroyed.

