### Neural correlates and corresponding outcomes related to craving and mental health

Specifically, we expect to provide preliminary positive results regarding a reduction in depressive symptomatology after an MT intervention, as indicated by lower scores on the Patient Health Questionnaire—9 [37] and increased resting-state FAA (higher left-sided frontally distributed power in alpha range [40, 41]); a reduction in anxiety symptomatology after an MT intervention, as indicated by lower scores on the Generalized Anxiety Disorder assessment—7 [42] and increased resting-state FMT [16, 44] and a reduction in short-term craving symptomatology after an MT intervention, as indicated by lower scores at the Brief Substance Craving Scale [45] and reduced power in the beta frequency band measured at rest [46]. The neural correlates of depressive, anxiety and craving symptomatology will be measured by means of resting-state EEG to investigate the intrinsic activity [63] of the brain and utilizing neurometric comparisons against a normative EEG database [16, 54]. In this way, we can examine the relationship between pre-post intervention changes in the multi-item questionnaires scores and pre-post intervention changes in the neural activity that is hypothesized to underpin depressive, anxiety and craving symptomatology. Since the experience of craving is related to a lack of control over intrusive drug-related thoughts [64, 65] and lack of behavioral control [66, 67], it can be approached with behavioral tasks requiring the deployment of inhibitory control functions (e.g., response inhibition) [11, 64]. The effect of MT on inhibitory control will be assessed using a behavioral task (Go/No-Go task), changes in the EEG event-related potential P3 and by measuring the correlation between inhibitory-related measures and short-term craving measures. It is expected to provide preliminary positive results regarding an improvement in inhibitory control after an MT intervention, as indicated by a higher accuracy in the Go/No-Go task and increased NoGo P3 event-related potential [47–49]. Furthermore, we expect a negative correlation between inhibition indexes (increased pre-post intervention NoGo-P3 brainwaves and higher pre-post intervention accuracy on NoGo trials) and scores in the BSCS. In other words, it is expected that an improvement in inhibitory control skills after an MT intervention would be associated with decreased subjective feeling of craving. A second measure to assess craving will be used. Since music represents an environmental cue, it can be associated with the drug experience and, potentially, induce craving by triggering emotional memories [68, 69]. Therefore, to monitor for instances of addiction memories that can possibly induce craving [15], an instantaneous single-item measure of craving will be collected before and after group and individual music therapy sessions. While MT has been suggested to reduce craving [30–32], the element of music itself, in some circumstances, can determine the induction of a craving state [68, 69] and there is no systematic empirical evidence about the mechanisms underlying the rising of moments of craving in MT sessions [4].

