
## Conclusion

With this feasibility study we aim to lay the groundwork for researching MT interventions in CSMTSs, addressing a gap of research into mechanisms of change regarding craving and related mental health outcomes. We propose a mixed-methods approach created with feedback from service users and practitioners addressing clinical practice and research needs. The procedures have been adapted to clinical practice and with this small-N feasibility study we aim to create an empirical base for a larger-N RCT drawing on ‘different disciplines and bring[ing] practitioners and researchers together’ to find out ‘what works to combat substance misuse, across supply, prevention, treatment and recovery’ [60].

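### The music therapy effect on secondary outcomes is evaluated by hypothesis tests in groups of 5 and at 10 v 5, with a confidence interval named only for correlations; estimates with intervals should lead instead

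*Protocol article*

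**What the plan says.** The abstract sets the size: "Fifteen participants, from a community service based in London, will take part in a mixed-methods non-blind randomized-controlled trial". Of the ten allocated to MT, "five of them will receive individual music therapy and five of them will receive group music therapy"; the other five receive ST only. Under Recruitment, if the group arm fills slowly, "the GMT sessions will start once at least 3 participants have been allocated".

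The section Analysis strategy regarding the secondary study aims concedes that "because of the small sample size, certain inferential statistics requirements cannot be satisfied" and concludes that "results related to the secondary aims are to be considered" preliminary. It then states: "Inferential statistical analyses will be conducted to evaluate the effect of MT (GMT/IMT) in addition to ST on mental health and brain processing". The named tools are:

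- a paired t-test in each of the three arms, with Wilcoxon signed-rank as fallback;
- an independent t-test of change scores, MT against ST, with Mann-Whitney as fallback.

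The same tests are repeated for resting-state EEG power. Means, SDs, graphs and, when they apply, effect sizes are also planned. A 95% confidence interval is named for the Pearson correlations and for nothing else.

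The last paragraph of Study aims and specific objectives lists directional expectations (b) to (d) for symptoms, treatment outcomes and inhibitory control. The Discussion adds that "we expect to provide preliminary positive results regarding a reduction in depressive symptomatology after an MT intervention".

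**The concern.** The article recognises a limit on inference and then uses tests as its stated way to evaluate the MT effect. At this size a test says very little. A non-significant result is the usual outcome even when a useful effect exists. A significant one can occur only when the observed difference is very large, which usually means that chance has inflated it. A mean, an SD and a p-value leave the reader to work out how much remains uncertain. A point estimate with an interval shows it directly.

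At stake is what can be said about expectations (b) to (d). The primary aim, feasibility and acceptability, rests on descriptive and thematic analysis and is not affected.

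**Working it through.** The article gives no power, significance level, effect size or SD for these outcomes, so there is no stated figure to reproduce.

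**Inputs.** From the article: arms of 5, 5 and 5, and MT pooled against ST as 10 v 5. Assumed: two-sided 5% level, normal change scores, equal variances, and true effects d of 0.3, 0.5 and 0.8 SD of the change score.

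**1. Threshold and interval width, 10 v 5.** The degrees of freedom are 10 + 5 − 2 = 13, with critical t = 2.160. The standard error factor is √(1/10 + 1/5) = 0.548. The product, 2.160 × 0.548 = 1.18 SD, is both the half-width of the 95% interval and the smallest observed difference that is significant.

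**2. Power and exaggeration, 10 v 5.** Power comes from the noncentral t distribution with noncentrality d/0.548. Exaggeration is the mean absolute effect among significant results divided by the true effect, from 300,000 simulated trials. The standardised ratios are 1.51/0.3, 1.55/0.5 and 1.62/0.8.

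| True d | Power | Raw difference, ratio to truth | Standardised effect, ratio to truth |
|---|---|---|---|
| 0.3 | 8.0% | 4.2 | 5.0 |
| 0.5 | 13.5% | 2.6 | 3.1 |
| 0.8 | 27.3% | 1.8 | 2.0 |

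Power of 80% needs d of about 1.66. Without selection on significance, the mean raw difference is unbiased (ratio 1.0).

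**3. If each MT arm were compared with ST separately (5 v 5).** The threshold rises to 1.46 SD, power at the same three effects is 7%, 11% and 20%, and the raw ratios are 4.6, 2.9 and 2.0.

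**4. Paired t-test, n = 5.** The threshold is 2.776/√5 = 1.24 SD of the change. Power is 8%, 14% and 28%.

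**5. Exact Wilcoxon signed-rank.** The smallest two-sided p is 2/2ⁿ.

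- n = 5: 2/32 = 0.0625
- n = 4: 2/16 = 0.125
- n = 3, the minimum at which the group arm may start: 2/8 = 0.25

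None can reach 0.05, whatever the effect. The uncorrected normal approximation can appear to do so at n = 5: z = 7.5/√13.75 = 2.02, p = 0.043. That reflects the approximation failing at this size and adds no information. Mann-Whitney at 10 v 5 is not limited in this way: its smallest p is 2/C(15,5) = 2/3003 = 0.0007.

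**6. What an interval would show.** An observed d of 0.5 at 10 v 5 has a noncentral-t 95% interval of about −0.60 to 1.58, compatible with no effect and with a very large one.

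**7. Small-sample correction.** Hedges' factor at 13 df is 1 − 3/(4 × 13 − 1) = 1 − 3/51 = 0.94, so an uncorrected standardised effect runs about 6% high even without selection.

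**The case against.** The strongest reply is that the article is already cautious and that much of the harm depends on how results are used.

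- **The concession is partial.** The article says that certain requirements fail. A reader might infer that it disowns inference altogether and so contradicts itself. It does not: offering non-parametric fallbacks and calling the results preliminary is consistent with a partial concession.
- **No decision rule is stated.** There is no significance level or threshold for these tests, so a pass-or-fail verdict is inferred from the choice of tests. Exaggeration arises only if results are selected or judged by significance.
- **Caution is promised.** Effect sizes and graphs are planned, and the section Sample size and dosage commits to careful, preliminary interpretation.
- **This is a condensed article.** A fuller plan may specify intervals.
- **A t-based interval rests on the same assumptions as the t-test.** It does not cure non-normality.

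A reader might also infer that an inflated estimate will be used to size the next trial, since the Conclusion says "we aim to create an empirical base for a larger-N RCT". The documents do not support that. No section says an effect estimate will be used for sizing, and the Discussion names the feasibility results as what will inform larger studies.

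All of these points limit the claim. They do not remove it: the article states how the effect will be evaluated, and the stated means is testing. Its cautions tell readers to be careful without showing how wide the uncertainty is.

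**Conclusion.** The point holds in a conditional form. Evaluating MT effects by these tests makes a reported effect likely to be exaggerated if significant and liable to be misread as absent if not. At a true effect of 0.5 SD, about 86% of trials of this size would miss it (100% − 13.5%), and the significant ones would overstate the raw difference 2.6-fold on average; the ratio falls to 1.8 at 0.8 SD and rises to 4.2 at 0.3 SD. The exact within-arm Wilcoxon fallback cannot reach 5% at all. These figures rest on the assumed two-sided 5% level, the assumed effects, full recruitment and 10 v 5. Fewer participants or separate 5 v 5 comparisons make them worse. The weakness is in how secondary results are evaluated and reported; it does not undermine the feasibility trial.

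**What to change.** In Analysis strategy regarding the secondary study aims, for questionnaires, task and EEG outcomes alike:

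1. Make the main result for each outcome the MT-minus-ST difference in change with its 95% confidence interval. Give within-arm changes with 95% intervals as description only.
2. Where a non-parametric method is used, give a matching interval such as Hodges-Lehmann. At n = 5 the exact Wilcoxon interval reaches at most 1 − 0.0625 = 93.75%, so state the level attained.
3. Where an effect size is given, use Hedges' g with its interval.
4. State that neither a significant nor a non-significant p-value will be taken to support or refute expectations (b) to (d) in Study aims and specific objectives.

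The cost is a few sentences of analysis and reporting text. No data collection or comparison changes; outcomes handled non-parametrically need the interval in item 2. The small downside is that the results paper can no longer headline significant improvements.

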## Methods

### Study aims and specific objectives

The main aim of this study is to test the feasibility of implementing individual music therapy (IMT) and group music therapy (GMT) as an intervention for service users (SUs) experiencing symptoms of depression and/or anxiety and engaged with CSMTSs. In order to approach the primary aim, our objectives are (I) to measure qualitative data on SU satisfaction with the MT program, (II) to measure retention in treatment and (III) to collect their feedback over the course of the treatment. The secondary aims of this project are to examine the feasibility of applying a pre-test, posttest, and in-session assessment battery as well as to measure the effects of MT (GMT and IMT) on mental health and the neural processing associated with it. We aim to explore the effects of MT in addition to standard treatment (ST) versus standard treatment alone. Further secondary aims concern the exploration of features of the therapeutic relationship and the role of music technology in the delivery, recording, and analysis of music therapy sessions. In order to approach the secondary aims, our objectives are: (I) To measure the effects of MT in addition to ST on the following treatment outcomes in comparison to ST alone: (a) substance use, (b) physical, mental wellbeing and quality of life, (c) retention in treatment, (d) engagement with treatment, (e) completion rate, (f) emotional processing, (g) psychological symptomatology. (II) To measure reduction in craving intensity after single MT sessions. (III) To compare the effect of MT in addition to ST versus ST alone on craving, inhibitory control, depression, anxiety and the respective associated neural signatures. (IV) To explore the perceived therapeutic alliance in IMT sessions. (V) To explore the neural dynamics of emotional processing during IMT sessions. (VI) To explore SU experiences of using music technology in an MT intervention. (VII) To explore how music technology can be utilized in the subsequent analysis of audio data of musical interaction recorded during MT sessions.

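### The stated route to a music-therapy effect is a pre–post test inside each arm, and no MT-versus-ST comparison is named for inhibitory control

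*Protocol article*

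**What the plan says.** The Abstract gives the arm sizes: of the ten MT participants, "five of them will receive individual music therapy and five of them will receive group music therapy", and "a further five participants will act as a control group receiving standard treatment only". Under Study aims and specific objectives, secondary objective III is "To compare the effect of MT in addition to ST versus ST alone on craving, inhibitory control, depression, anxiety", together with the associated neural signatures.

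Under Analysis strategy regarding the secondary study aims, the article does the following.

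- **All secondary outcomes.** The sentence on inferential analysis says the effect of MT in addition to ST will be evaluated by "comparing the data between pre- and post- intervention in each group using a parametric or non-parametric test", with the paired t-test and the Wilcoxon signed-rank test as examples. P3 amplitude and Go/No-Go accuracy are the fifth item in the list of dependent variables.
- **Questionnaires.** A pre–post comparison "will be performed for each group (GMT, IMT and ST) with a paired-samples t-test", with Wilcoxon as fallback. Difference scores in the MT groups are then compared with those in the ST group by independent t-test, with Mann–Whitney as fallback.
- **Resting-state EEG.** For the pre–post difference "in the topographic distribution of EEG power in the selected frequency bands a paired-samples t-test will be performed for each of the three groups", again with Wilcoxon as fallback. An MT-versus-ST comparison of power follows, by independent t-test or Mann–Whitney.
- **Inhibitory control.** The only analysis specific to it is a correlation of changes in P3 amplitude and no-go accuracy with change in the craving scale.

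Arms may be smaller than five. Under Recruitment, if five are not found within two months, "the GMT sessions will start once at least 3 participants have been allocated". For individual therapy, "We will only re-recruit twice before continuing with the remaining IMT participants". Under Sample size and dosage, a participant who misses the week 8 battery has the baseline value carried forward.

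**The concern.** The trial randomises a control arm so that change under MT plus ST can be set against change under ST alone. The sentence that says how the MT effect will be evaluated does not use that arm as a comparator. A pre–post change within an MT arm also contains:

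- the effect of ST, which every arm receives;
- the passage of time;
- possible regression to the mean, since reporting depressive or anxiety symptoms is an entry criterion;
- for the Go/No-Go task, practice from doing it twice.

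For questionnaires and resting-state EEG power, a between-arm test is also planned, so the right contrast will exist beside the wrong one. For inhibitory control the within-arm test is the only effect test that is specified, and practice threatens this outcome most directly. Objective III is then not answered for it, and an improvement in accuracy or P3 amplitude in an MT arm could be reported as an MT effect without reference to the controls.

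Separately, the within-arm fallback is a rank test on at most about five pairs. Its p-value can take few values, and the smallest of them is large.

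**Working it through.** The article states no power, effect size or significance level for these outcomes, so there is no figure of its own to reproduce.

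**1. Which outcomes have a named MT-versus-ST test**

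| Secondary outcome | Within-arm test | MT-versus-ST test |
|---|---|---|
| Questionnaire scores (PHQ-9, GAD-7, BSCS, TOP) | yes | yes, on difference scores |
| Resting-state EEG power | yes | yes |
| P3 amplitude | yes (general sentence) | none named |
| Go/No-Go accuracy | yes (general sentence) | none named |

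The first between-arm test is worded for questionnaires and the second for the topographic distribution of power in the selected bands. Neither wording reaches an event-related potential amplitude or a behavioural score.

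**2. Floor of the Wilcoxon fallback**

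Inputs: five per arm (Abstract); as few as three in group therapy at the start (Recruitment). With n non-zero, untied differences all in one direction, the exact two-sided p is 2/2^n.

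- n = 5: 2/32 = 0.0625
- n = 4: 2/16 = 0.125
- n = 3: 2/8 = 0.25

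A participant with baseline carried forward has a difference of zero. In the usual form of the test zeros are dropped, so each such participant lowers n by one.

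Variants at n = 5: exact one-sided 0.031; two-sided normal approximation 0.043 without and 0.059 with continuity correction. The floor above 0.05 therefore belongs to the exact two-sided test.

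**3. How misleading within-arm tests can be (illustration)**

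Assumptions: two-sided 5% level, paired t-test, five per arm, independent observations, and the same standardised change in all three arms, so no MT effect. The power of one arm's test is 0.281 at a change of 0.8 SD and 0.401 at 1.0 SD. The chance that at least one MT arm is significant while ST is not equals [1 − (1 − p)²] × (1 − p).

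- Change 0.8: (1 − 0.719²) × 0.719 = 0.483 × 0.719 = 0.35
- Change 1.0: (1 − 0.599²) × 0.599 = 0.641 × 0.599 = 0.38

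Under these assumptions, about a third of trials with no MT effect would show that pattern for a given outcome.

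**4. What the between-arm comparison offers**

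The smallest exact two-sided Mann–Whitney p is 2/C(15,5) = 2/3003 = 0.00067 for both MT arms pooled against ST (10 versus 5), and 2/C(10,5) = 2/252 = 0.0079 for 5 versus 5. The floor is no longer an obstacle. Power is still low: at 10 versus 5 an independent t-test needs a standardised difference of about 1.66 for 80% power at an assumed two-sided 5% level.

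**The case against.** The strongest reply is that the plan does contain between-arm comparisons. The secondary-aims section opens by announcing MT plus ST compared with ST only across the secondary variables, then names tests of exactly the right kind for questionnaires and EEG power. This stands. A reader might infer from the evaluating sentence that MT effects are judged throughout from within-arm tests, and the article does not support that reading. The fault is confined to that sentence and to inhibitory control.

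It can also be said that the missing test for P3 and accuracy is a detail for a fuller document. This stands only in part. The opening sentence shows the intent, but the article goes on to specify what is done with these variables, and what it specifies is a within-arm test and a correlation.

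A reader might also infer that the fallback can never give p below 0.05. That goes too far, because the article fixes neither sidedness, nor the exact or asymptotic form, nor a significance level, and its hypotheses are directional. Likewise, the article names no particular normality test and does not say that topography is tested electrode by electrode. Error rates built on those procedures would describe something the plan does not state.

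Finally, the article says openly that the small sample prevents some inferential requirements from being met, and it labels the secondary results preliminary. That covers imprecision. It does not cover a contrast that would be biased for the MT effect at any sample size. It is fair to add that the article nowhere says that a significant MT arm beside a non-significant ST arm will be taken as an effect. The illustration shows a risk, not a stated rule.

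**Conclusion.** The point holds in limited form. The article ties evaluation of the MT effect to within-arm pre–post tests, which cannot separate MT from ST, time, regression to the mean or task practice. For P3 amplitude and Go/No-Go accuracy no MT-versus-ST comparison is named, so objective III is not delivered for inhibitory control. For the questionnaires and resting-state EEG power the right comparison is already planned.

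The Wilcoxon floor of 0.0625 is exact for five non-zero differences and a two-sided exact test. That it precludes significance rests on an assumed two-sided 5% level. The figures of 35% and 38% rest on the assumptions listed with them.

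All of this concerns secondary outcomes that the article presents as preliminary. The primary feasibility aim, analysed descriptively and thematically, is not touched.

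**What to change.** 1. Reword the evaluating sentence so that any MT effect is judged from the between-arm difference in pre–post change (MT plus ST versus ST alone), reported as an estimate with a 95% CI.
2. Extend that comparison explicitly to P3 amplitude and Go/No-Go accuracy.
3. Present within-arm changes descriptively (mean or median change, SD, individual plots) and say that they are not evidence of an MT effect.

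No new data are needed, since all three arms complete the same battery at baseline and week 8. The cost is a few lines of text and the loss of within-arm p-values. The intervals will be wide: at 10 versus 5, assuming equal variances, the half-width is 2.16 × √(1/10 + 1/5) = 2.16 × 0.548 = 1.18 SDs of the change score. That is a fair picture of what 15 participants can show.
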